#### Sample size

The sample size was calculated for a t test comparing the IG and the CG regarding guideline compliance to EBHI as measured by MAPPinfo. It is assumed that MAPPinfo is normally distributed with the same standard deviation (*σ*) of 10% in both groups. Pretest data from MAPPinfo showed very low ratings for online-available health information. The quality of this information could be improved with just a little effort. Based on these assumptions and a sample size of 26 provider groups (13 in each study group), a quality improvement of 1.5* *σ* corresponding to a very strong Cohen’s effect size can be detected with 90% power using a two-sided significance level of 5% after excluding at the most 10% dropouts. The power was calculated using the statistical software package SAS version 9.4 (PROC POWER).

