**Fig. 3 Fig3:**
[figure not shown]
Standard Protocol Items: Recommendations for Interventional Trials (SPIRIT) Figure

Completed health information can be sent to the study team at any time. After 10 months, the development process should be concluded and the providers will be asked for the material. A provider who cannot deliver after 10 months can be given a 2-month extension of the deadline. The provider should give a justification for the delay and a reasonable timeline for the following 2 months.

After 12 months (*t*_2_), even unfinished material must be submitted. The information will be rated with regard to the primary outcome. Single criteria (or else the entire information) that do not meet the MAPPinfo requirements, are coded as zero. Providers of both groups (IG and CG) who completed their information will be asked to give further information on the development process (*t*_3_). Interviews will be conducted in the IG to explore barriers and facilitators of implementation (cf. process evaluation). The providers in the CG will be invited to make appointments for the training programme (*t*_3_). After the provided information has been rated, providers may receive individual feedback on their material. This is optional, but this way the feedback would benefit especially the providers in the CG.

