**Fig. 4 Fig4:**
[figure not shown]
Data flow

Withdrawal from the study is possible at any time without giving reasons and without disadvantages for the participants. In the case of withdrawal, data can be deleted only before anonymisation (after completion of the analysis). Privacy and data protection will be taken into account according to the German Data Protection Act [37]. A unique code number will be assigned to every participant. All data will be marked with this code number and, thus, pseudonymised. Identification of single participants is only possible with the coding key, which is stored on password-protected servers at the Martin Luther University Halle-Wittenberg. Only the project team has access to the coding key which is protected securely from third parties. Once data analysis has finished, the coding key will be deleted. From then on, data can no longer be deleted in the case of withdrawal from the study.

All data provided by the study participants are treated as absolutely confidential. Researchers adhere to the data protection rules. All data will be stored on password-protected servers and there will be no disclosure to third parties. Publication and storage of data will only be performed in an anonymised form. Audio-recordings will be deleted after transcription. Data will be stored at the Martin Luther University Halle-Wittenberg for 10 years.

The primary analyses will be performed from the intention-to-treat (ITT) perspective. The provider’s characteristics (institutional and individual level) will be analysed descriptively. Baseline variables of individuals will be described on the individual level by means, standard deviations, percentiles and frequency tables, depending on their distributions. The IG and CG will be described separately.

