The primary outcome will be analysed on the provider level assuming approximately normal distribution by comparing means between the IG and CG using the *t* est. The distribution of MAPPinfo will be described graphically. In case of deviations from the normal distributions, transformations or alternative tests will be discussed as secondary sensitivity analyses. Frequencies of missing values will be described in detail. Multiple imputations will be performed for the primary outcome if there is enough information available. Only a few missing values are expected because the coding by the raters is very dependable. Incomplete health information will be considered and analysed as non-missing. The imputations will be performed if three values or fewer (12%) of the primary outcome (the outcome score, not the single items) are missing. The multiple imputation model will be fitted using the baseline variables of providers. For the binary secondary outcomes, relative frequencies will be described in both provider groups and compared using Fisher’s exact test. A secondary per-protocol analysis will be performed as a complete case analysis (without multiple imputations for the primary outcome). The secondary per-protocol analysis is planned to compare the results between ITT and per-protocol and to discuss a possible bias from protocol violations and missing values.

A data monitoring committee will not be necessary as the trial does not involve a high-risk intervention and participants do not belong to a vulnerable population. We do not expect adverse events or other unintended effects of the intervention. During the entire study period, participants will be able to contact the study centre, if necessary.

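### The imputation rule for the primary outcome does not name randomised group, stops above three missing scores with no stated ITT method, and leaves non-delivery unclassified

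*Protocol article*

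**What the plan says.** In the protocol article, under Data management, protection and analyses, the analysis principle is: "The primary analyses will be performed from the intention-to-treat (ITT) perspective". The primary test is a t test on provider-level MAPPinfo scores. Missing scores are to be multiply imputed if enough information is available, and with a numerical limit: "The imputations will be performed if three values or fewer (12%) of the primary outcome (the outcome score, not the single items) are missing". The predictors are given in one sentence: "The multiple imputation model will be fitted using the baseline variables of providers". The section Baseline data lists those variables: institutional and individual characteristics, baseline MAPPinfo and critical health literacy. Randomised group is not among them.

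The reason for expecting little missingness is: "Only a few missing values are expected because the coding by the raters is very dependable". Incomplete material counts as observed. Complete-case analysis is assigned only to the secondary per-protocol analysis, which is to be set against the ITT result in order to discuss bias from protocol violations and missing values.

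The section Procedure requires unfinished drafts to be handed in at 12 months and adds: "Single criteria (or else the entire information) that do not meet the MAPPinfo requirements, are coded as zero".

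**The concern.** There are three linked problems.

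- **Imputation model.** Baseline variables are measured before allocation, so they carry no information about the arm. A model built only on them gives a missing IG score and a missing CG score the same expected value, apart from chance baseline differences. The imputed data then show a smaller difference than the observed data.
- **Cut-off.** Above three missing scores imputation stops, and no primary method takes its place. The obvious default is complete cases. Missing scores would then be handled as in the secondary per-protocol analysis, and comparing the two could no longer show bias from missing data.
- **Non-delivery.** Dependable raters do not prevent withdrawal or failure to deliver. Since drafts count as observed, these are the main routes to a missing score. The Discussion itself foresees compliance problems, including in producing the material. Recruitment foresees possibly greater effort in the IG, and under Procedure the IG starts production only after training. Missingness could therefore be informative and could differ by arm.

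With 13 providers per arm, two or three scores can move the primary result.

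**Working it through.** **Inputs (Sample size section).** "The sample size was calculated for a t test comparing the IG and the CG"; "standard deviation (*σ*) of 10% in both groups"; "a quality improvement of 1.5" SD, i.e. 15 points; 13 providers per arm; two-sided 5%; 90% power after at most 10% dropout.

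**Plan's own figure.** Exact t-test power (noncentral t) at 1.5 SD is 88.7% with 10 per arm and 91.7% with 11 per arm. The requirement is therefore 11 per arm, and 11/0.9 = 12.2, rounded up to 13. The planned 26 is reproduced and the power statement is sound. The stated 12% is also right: 3/26 = 11.5%.

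**Effect of leaving group out.** Take the CG mean as origin. Let a and c be the numbers observed in IG and CG. The pooled observed mean is p = 15a/(a + c). If missing scores are imputed around p, the expected difference is [15a + (13 − a)p]/13 − (13 − c)p/13.

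- One missing, IG: p = 180/25 = 7.2; difference = 187.2/13 = 14.4.
- One missing per arm: p = 180/24 = 7.5; difference = 187.5/13 − 7.5/13 = 13.85.
- Three missing, IG: p = 150/23 = 6.52; difference = (150 + 19.57)/13 = 13.04.
- Two IG and one CG missing: p = 165/23 = 7.17; difference = (165 + 14.35)/13 − 7.17/13 = 13.24.
- Three missing, CG: p = 195/23 = 8.48; difference = 15 − 3 × 8.48/13 = 13.04.

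**Simulation.** 3,000 trials per case; true difference 15, SD 10; scores missing completely at random; Bayesian linear-regression imputation with 20 imputations; Rubin's rules with small-sample degrees of freedom. One baseline covariate has an assumed correlation of 0 or 0.5 with the outcome, and the ranges below span these two values. Each cell gives mean estimate; power.

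| Missing IG, CG | Group omitted | Group included | Complete cases |
|---|---|---|---|
| 1, 0 | 14.37–14.52; 93.1–93.5% | 14.96–15.11; 94.7–94.8% | 14.97–15.11; 94.8–95.0% |
| 1, 1 | 13.85–13.90; 89.5–90.1% | 15.00–15.06; 93.5–94.2% | 14.99–15.05; 94.0–94.4% |
| 3, 0 | 12.95–13.17; 82.5–83.7% | 14.90–15.15; 91.7–92.3% | 14.91–15.13; 91.8–92.9% |
| 2, 1 | 13.26–13.34; 84.2–85.9% | 15.04–15.11; 91.8–93.5% | 15.04–15.12; 93.1–93.4% |
| 0, 3 | 13.00–13.13; 81.9–83.6% | 14.95–15.10; 90.9–92.3% | 14.96–15.09; 92.4–92.6% |

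Arithmetic and simulation agree, and a covariate correlated 0.5 with the outcome does not remove the shrinkage.

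**How often the cut-off would bite.** Assume independent missingness with probability 0.10 per provider. For 0, 1, 2 and 3 missing of 26, the probabilities are 0.0646, 0.1867, 0.2592 and 0.2304, which sum to 0.741. So P(four or more) = 0.259. At 5% it is 0.04, at 15% 0.56 and at 20% 0.79.

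**Non-delivery: zero or imputed.** Let m be the CG mean, which the article does not give. For one IG non-deliverer, imputing instead of scoring zero raises the IG mean by (m + 7.2)/13 if group is omitted, or (m + 15)/13 if it is included. For assumed m of 20, 30 and 40 this is 2.1, 2.9 and 3.6 points, or 2.7, 3.5 and 4.2 points: 14% to 28% of the 15-point target.

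**The case against.** A reader might infer that group is deliberately excluded from the model. The text does not say so: group is not named, but it is not ruled out, and imputation by arm remains possible. An analysis plan that is not shown may settle this. That stands, so the shrinkage is conditional on following the sentence as written. It is also bounded, small with one or two missing scores, and works against the trial's hypothesis, so it could not produce a false positive result.

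A reader might also infer that the cut-off contradicts the ITT principle. It does not. No complete-case fallback is stated for the primary analysis, so what happens above three missing is undefined. Complete cases compared by randomised arm are unbiased if scores are missing completely at random, and in the simulation they lose almost nothing. The cut-off also sits close to the planned dropout ceiling (10% of 26 is 2.6), and the 26% figure treats that ceiling as the expected rate and every dropout as a missing score.

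Finally, a reader might conclude that delivering nothing is rewarded over delivering something poor. The article never says non-delivery is imputed, and the zero-coding sentence in Procedure could be meant to cover it. An effect on the mean from IG non-delivery would be offset by non-delivery in the CG.

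The plan does describe missing values in detail and compares ITT with per-protocol results. Above three missing, however, that comparison has no stated difference in how missing scores are handled, which is the contrast it needs.

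**Conclusion.** The point holds in a limited form. The one sentence on the imputation model names predictors that do not include group. Followed literally, with three scores missing, it turns 15 points into about 13 and costs roughly 6 to 10 percentage points of power against a model with group. The loss is about 0.6 point with one missing and just over 1 point with two. These sizes rest on the protocol's SD and target effect, on scores missing completely at random, and on a baseline correlation between 0 and 0.5. Under the same conditions the literal rule does worse than no imputation.

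Above three missing scores the primary ITT handling is undefined. At an assumed 10% chance per provider this would arise in about a quarter of trials. The rationale based on rater dependability does not address withdrawal or non-delivery, and the sections Procedure and Data management, protection and analyses leave open whether non-delivery is a zero or a missing value. The documents do not support saying that group is excluded, that ITT is contradicted, or that non-delivery is rewarded.

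**What to change.** Before the primary scores are analysed:

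1. State that the imputation model includes randomised group (or that imputation is done separately by arm) and the baseline MAPPinfo score.
2. Replace the limit of three missing scores with one primary method that applies to any number missing.
3. Reconcile the sections Procedure and Data management, protection and analyses by saying whether a provider with no ratable item at 12 months scores zero or is missing.
4. Add a pre-specified sensitivity analysis in which every such provider scores zero.

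A tipping-point analysis would be a useful option but is not essential. The cost is a few sentences of wording and a little extra analysis. No additional data are needed.

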#### Process evaluation

To support future implementation of the *guideline evidence-based health information* and the training programme, a comprehensive analysis of the underlying processes of this complex intervention is indispensable [38]. Barriers and facilitators of implementation should be assessed. Additionally, the high quality of the training programme should be ensured. We will focus on parameters such as recruitment, reasons for participation or non-participation, intervention fidelity, structure and process-related factors, attitudes toward the intervention, response of individuals and organisations, and unintended consequences [38, 39]. Mixed methods will be applied [40] according to the MRC framework for process evaluation of complex interventions [38].

Structured documentation will be used to assess data of recruitment and intervention fidelity (e.g. recruitment process; numbers of institutions invited, responses and participants in each training session; location, time and duration of the training; completeness of modules and online tasks and reasons for deviations; and unexpected difficulties). Feasibility and acceptance of the training programme will be assessed at the end of the training sessions using structured feedback, and all statements will be documented. Critical health literacy will be assessed using the CHC test [36] after the IG and CG have completed the training programme.

To map the development process and the methodological quality of the produced health information, all the providers (IG and CG) will be asked to provide the MAPPinfo self-declaration after completing the health information. The self-declaration comprises free-text questions on the selection of the reported options and outcome measurements, search strategies, methods of data extraction and critical appraisal, reasons for the use of pictures, graphics, fact boxes, value clarification tools, animations and interactive tools. Experts will review the results and, if there are outstanding issues, interviews will be conducted. In addition and to identify influencing factors, the resources and support used in the development process as well as any training attended during the study period will be assessed.

In the IG (theoretical sampling), semi-structured interviews will be conducted with single participants as well as with persons in charge in order to explore the implementation barriers and facilitators. Relevant factors for acceptance and usability of the educational contents and materials may be further assessed. In particular, the use of educational contents in daily routines and barriers against putting the guideline recommendations into practice will be explored. If the participant consents, interviews will be audio-recorded and then transcribed.

Data will be collected at various time points. An iterative process of collecting and analysing qualitative data will allow the exploration of unexpected aspects in further interviews [38]. Data will be analysed in accordance with the method of collection [40]. Descriptive statistics will be used for quantitative data. For qualitative data, a qualitative content analysis according to Mayring will be performed [41].

## Discussion

The aim of the proposed trial is to evaluate the efficacy of the *guideline evidence-based health information* in combination with a training programme for providers of health information in comparison to having access to the guideline on its own. We expect the combined intervention to improve the quality of health information and thus promote informed patient decisions.

However, the training programme is extensive and time consuming; it does not only provide guidance on the application of the guideline but also extensive ebm knowledge. That is because a previous qualitative study revealed the providers’ shortcomings regarding their ebm competences. Participants must be released from their work duties in order to attend the training and, in addition, the development of information in compliance with the guideline recommendations is time and cost-intensive, e.g. comprehensive literature searches must be conducted by the providers themselves or contracted out. The lack of access to databases or references can constitute a further barrier. These potential barriers may limit the study results because of problems in recruitment and study compliance (attending the training programme in person and online; producing information in accordance with the requirements). To address the barriers, the providers will receive comprehensive information on the study course and its requirements, incentives will be provided (publicity for providers of high quality information) and the providers will receive support for purchasing literature. The attitudes of the providers regarding EBHI will play a crucial role and, therefore, these attitudes will be addressed in the training programme and additionally in the workshop for the providers in charge of health information publications. The freedom of choice regarding the topic of the information to be delivered as a working sample might lead to increased internal variance and, therefore, make it more difficult to detect an intervention effect. On the other hand, this method will safeguard both the motivation of the participant to cooperate and the ecological validity. As experience shows the variability on the quality spectrum to be also quite low between topics, we are nevertheless optimistic of being able to demonstrate an effect, even if the small sample size of providers can detect only strong effects of the intervention and limits detailed secondary analyses.

After efficacy is proven, the training programme should be established as a continuous offer for providers of health information in order to enhance their ebm competences and to ensure high-quality EBHI in the long term.

## Dissemination

All the results of the study (including negative ones) will be published in international and open-access journals and presented at meetings and congresses. According to the recommendations of the International Committee of Medical Journal Editors (ICMJE), only persons directly involved in the study will be designated as authors [42].

All the participants will receive an abbreviated version of the final report in language written for laypersons.

## Trial status

Protocol version 2, 26 June 2019.

Date recruitment began: 26 July 2019; approximate date when recruitment will be completed: 31 August 2020.

## Data Availability

The study centre will coordinate the intra-study data sharing process. The data sets will be available for all the principal investigators. After study completion, the adjusted data will be stored and made publicly accessible via a special data repository to fulfil national [43] and international [44, 45] requirements for sharing clinical trial data. For this purpose, the European Open Science Cloud (EOSC), a collaborative tool for data sharing and reuse, was recently implemented to serve all researchers from all research domains [46].

## Abbreviations

CG: Control group
DNEbM: *Deutsches Netzwerk Evidenzbasierte Medizin*
EBHI: Evidence-based health information
ebm: Evidence-based medicine
GMC: General Medical Council
GPGI: *Good practice guidelines for health information*
GRADE: Grading of Recommendations Assessment, Development and Evaluation
IG: Intervention group
MAPPinfo: Mapping Health Information Quality
MRC: Medical Research Council
RCT: Randomised controlled trial
SPIRIT: Standard Protocol Items: Recommendations for Interventional Trials
